#### 2.4.2. Secondary Outcomes

The secondary outcomes include changes in: (1) physical activity; (2) anthropometric measurements and body composition; (3) physical capacities; (4) well-being. In addition, psychological mediators will also be examined.

The following criteria will be used in order to measure the WISE program adherence [42]:Retention (completion): the participants following the WISE exercise videos and showing up to the follow-up measurements.Attendance: percentage of videos completed of the total of 50 videosDuration: adherence to a minimum of 20 min of exercise two times a week.Intensity: intensity levels of the sessions will be assessed at the end of each session using the modified Borg Scale, which measures perceived exertion [43].

These items will be measured through a weekly online exercise diary, where the participants will be asked if they completed both video sessions. They will also be asked about their perceived exertion after each session. This will allow us to assess whether they are following the 20 min of exercise two times a week rule, completing the video sessions, so we can see the number of videos completed at the end of the program.

Table 1 presents the assessment schedule, following the Standard Protocol Items: Recommendations for Interventional Trials (SPIRIT) schedule template. Table 5 provides an overview of all the outcome measures.

## 3. Statistical Analyses Plan

All the statistical analysis will be performed using the SPSS version 24 Software (SPSS Inc., Chicago, IL, USA). If adherence issues occur, all analyses will be evaluated by intention-to-treat principles, with a level of significance of 0.05. Continuous outcomes will be presented using mean and standard deviation if they follow a normal distribution. On the other hand, count outcomes, such as WISE sessions completed, will be reported through the median and percentage of achievement. At the basal assessment, an independent-samples Student’s *t*-test will be performed to rule out differences between groups of age and height of participants.

In order to answer the first aim of this study, the changes in the adherence variables, such as daily steps, the Borg scale and the IPA questionnaire, will be analyzed by 1-within-subject factor multivariate analysis of variance (MANOVA). The Bonferroni adjustment will be used for post-hoc comparisons between the T0, T1 and T2 times assessments. On the other hand, the secondary outcomes of the study will be tested by 2-factor mixed MANOVA to analyze the effects of a within-subject factor (time assessment from T0 to T4), the between-subject factor (group) and their interaction. As mentioned above, Bonferroni adjustment will be used for times and groups comparisons. In addition, the same statistical test will be carried out considering the country of origin of the data as a covariate, and the findings will be reported according to their statistical significance. For all the statistical analyses, differences will be declared statistically significant if the *p*-value is less than 0.05. The exact *p*-value and 95% confidence interval will be reported.

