#### 2.2.4. Randomization, Allocation and Blinding

After the first experimental visit (T0), the participants will be randomized using a computer-generated randomization list into one of the two conditions with a 1:1 allocation. The allocation will be transmitted using numbered (0 = control/1 = Intervention), opaque and sealed envelopes, which will be given to the young women and then registered by the data collectors. The assessors will be blinded to the treatment allocation, although double blinding is not applicable in interventions of this nature as it is impossible to conceal the allocation from the participants. The participants will be instructed not to reveal their allocation to the assessors to ensure unbiased assessment.

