### 2.3. Intervention

#### 2.3.1. Procedure

All participants will undergo a total of four visits, including the initial inclusion visit and three experimental visits (T0, T1 and T2), as detailed in Table 1. During the selection visit, qualified personnel will make sure that the young women fulfil the inclusion criteria and that they (or their parent/legal representative in case the girl was a minor) sign the informed consent form after explaining the project itself and after responding to all of their questions. One week after the initial visit, the T0 experimental visit will be conducted to measure all of the baseline assessments before the start of the intervention. At the halfway mark of the program (i.e., three months in), a mid-term measurement will be carried out, denoted as T1. The T2 experimental visit will be scheduled at the end of the program (i.e., after six months of intervention). The three experimental sessions will be identical.

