2.Education in healthy habits: once a week, the participants will receive reading material, with an approximate duration of 2 to 5 min, on general advice on nutrition, sleep (Figure 2B) and well-being (Figure 2C), written by experts in the field. Dietary guidelines will also be created by a team of professionals specialized in nutrition to stimulate the participants and give them basic indications on proper eating behavior. These reading materials will be delivered to the participants through the WISE application and will appear by means of a push notification. The complete list of messages for the WISE participants can be seen in Table S2.3.Activity tracker: participants will be able to check their activity at any time of the day through the Xiao Mi Band 5 smartwatch (Figure 2D). The data will also be displayed in the app with weekly charts so participants can see their progression. The participants will also be able to track their weight and their sleep over time (Figure 2E) through the application. Moreover, their heart rate will be recorded. This tool aims to give feedback on behavior and promote self-monitoring of physical activity.4.Motivational activities: in order to motivate the participants to perform the videos, social media, email, WhatsApp groups and/or other channels, such as Viber (depending on the availability/popularity in each country), will be created for the participants to communicate with each other. In addition, social meetings will be organized through “Open Days” held in each country and transmitted through streaming so all the participants can attend the event. During the “Open Days”, talks on nutrition and physical activity will be held, as well as in-person meetings to perform the exercises. Moreover, the participants can expose their doubts and concerns, which can be solved in a personal manner during these events.

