BCTs, behaviour change techniques; WISE, Women’s Involvement in Steady Exercise; RCT, randomized controlled trial.

**Table 3 healthcare-11-01279-t003:** WISE exercise protocol progression.

Month	Session	Work Time	Recovery Time	Level
1	1	20”	20”	Initiation and no impact
	2			Medium-advanced with impact
2	1	20”	15”	Initiation and no impact
	2			Medium-advanced with impact
3	1	20”	10”	Initiation and no impact
	2			Medium-advanced with impact
From week 12th, we introduce 2 different intensity levels in each session (one without impact or less demanding) so the participants can choice between the 2 levels in order to better adapt their effort				
4	1	30”	20”	Medium
	2			Advanced
5 and 6	1	40”	15”	Medium
	2			Advanced

**Table 4 healthcare-11-01279-t004:** Summary of the groups’ content.

Intervention Group (Videos)	Control Group
50 HIIT video exercise sessions	Physical activity recommendations (at the start of the intervention: general physical activity guidelines) *
Communication group	--
Activity monitoring tool (mobile app + Xiaomi Mi Band 5)	Activity monitoring tool (Xiaomi Mi Band 5)
Education in healthy habits	--

HIIT, High Intensity Interval Training. * At the end of the program, the participants will have access to the HIIT video sessions.

**Table 5 healthcare-11-01279-t005:** Outcomes measures of the WISE RCT.

Outcome	Assessment Method
Primary outcome	
Daily step count over 6 months	The Xiaomi Mi Band 5 smartwatch will be used to assess the daily step count. Days with missing data and/or days with fewer than 1000 steps will be excluded from the analysis.
Secondary outcomes	
Physical activity	
Self-reported physical activity and sedentary behaviors	Self-reported behaviors will be gathered using the International Physical Activity Questionnaire (IPAQ). The IPAQ assesses walking and activities of a moderate and vigorous intensity that are performed continuously for at least 10 min in all domains of everyday life (i.e., leisure, occupational, household and transport) in the last 7 days. The IPAQ demonstrates acceptable levels of test-retest reliability and fair to moderate associations with accelerometer measures [40,41].
Anthropometric data and body composition	

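### The Borg scale is placed in a T0, T1 and T2 change analysis although it is rated only after video sessions, so no woman can have a T0 value

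*Protocol article*

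**What the plan says.** For the first aim, section 3 of the protocol article says that "the changes in the adherence variables, such as daily steps, the Borg scale and the IPA questionnaire, will be analyzed by 1-within-subject factor" MANOVA. The next sentence fixes the levels of the time factor: "The Bonferroni adjustment will be used for post-hoc comparisons between the T0, T1 and T2 times assessments". The model has no group factor; the two-factor mixed model is reserved for the secondary outcomes.

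Section 2.4.2 introduces Borg as the Intensity item, one of four criteria of programme adherence: "intensity levels of the sessions will be assessed at the end of each session using the modified Borg Scale". On collection it adds: "These items will be measured through a weekly online exercise diary, where the participants will be asked if they completed both video sessions", together with the exertion felt after each session.

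On timing, section 2.3.1 says that "the T0 experimental visit will be conducted to measure all of the baseline assessments before the start of the intervention", and section 2.2.4 that "After the first experimental visit (T0), the participants will be randomized". Section 2.3.2 gives the videos to the intervention group. The footnote to the control column of Table 4 says: "At the end of the program, the participants will have access to the HIIT video sessions".

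**The concern.** A within-subject analysis over T0, T1 and T2 needs a value at each of the three times. Borg, as the article defines it, is a reaction to a video session, and no video session has taken place by T0. The analysis section and the outcome section therefore contradict each other. This is more than a detail left to a fuller analysis plan, because the article itself names the variable, the model and the time levels.

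Two things are at stake. First, a named analysis under the first aim cannot be run as written. Second, Borg shares its sentence with daily steps, the primary outcome, and with IPAQ. If the three are fitted as one multivariate response, an empty Borg column at T0 could take the other two down with it.

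**Working it through.** The article gives no figure to reproduce for this point. The check sets when and in whom Borg is recorded against what the model requires.

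**Step 1: inputs**

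- Planned size: 300 women, 150 per group (section 2.2.2).
- Levels of the time factor: T0, T1 and T2 (section 3).
- T0 precedes both the intervention (section 2.3.1) and randomization (section 2.2.4).
- Borg is rated per session and gathered in a weekly diary about the two videos (section 2.4.2).
- The videos go to the intervention group; controls gain access after the programme (section 2.3.2 and Table 4).
- Table 1 has no row for Borg. It has an Adherence row whose duration line did not survive text extraction. Table 5 refers back to the session-based definition.

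**Step 2: Borg values that can exist**

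| Time | Intervention (150) | Control (150) |
|---|---|---|
| T0 | 0 | 0 |
| T1 | session ratings only, no stated rule linking them to T1 | 0 |
| T2 | session ratings only, no stated rule linking them to T2 | 0 |

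At T0 the count is 0 + 0 = 0 of 300. The lost line in Table 1 cannot alter this: exertion in a video cannot be rated before the video has been delivered.

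**Step 3: effect on the model**

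Complete cases over T0, T1 and T2 cannot exceed the number of women with a T0 value, so there are 0 for Borg.

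- *Separate models for each variable:* the Borg model has 0 cases; the steps and IPAQ models are untouched.
- *One joint model with listwise deletion:* a woman is kept only if all three variables are present at all three times. The Borg condition fails for everyone, so 0 cases remain for steps and IPAQ too.

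The article does not say which of the two is meant, nor how incomplete cases are handled in this model. The second result is therefore conditional.

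**Step 4: what Borg data do exist**

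With 50 videos per woman (Table 4), the intervention arm could supply up to 150 × 50 = 7,500 ratings at full attendance. The information on intensity is there; it does not have the form that the model needs.

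**Step 5: why those ratings should be shown by month**

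Share of work time from Table 3 = work / (work + recovery):

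| Month | Work / recovery (s) | Share |
|---|---|---|
| 1 | 20 / 20 | 20/40 = 50.0% |
| 2 | 20 / 15 | 20/35 = 57.1% |
| 3 (T1) | 20 / 10 | 20/30 = 66.7% |
| 4 | 30 / 20 | 30/50 = 60.0% |
| 5 and 6 (T2) | 40 / 15 | 40/55 = 72.7% |

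The share rises by 22.7 points from month 1 to months 5 and 6, with a dip in month 4. From T1 to T2 it rises by only about 6 points, although the work bout doubles from 20 to 40 seconds. The prescription is not constant, so one Borg average over the programme would mix different demands.

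**The case against.** The strongest reply is that little is lost. Section 2.4.2 defines the Intensity criterion as a level in the sessions, not as a change from baseline. The ratings are still collected, and section 3 provides for the presentation of continuous outcomes. Borg belongs to one of four adherence criteria listed under secondary outcomes, while the primary outcome is daily steps; neither the definition of that outcome nor the sample size depends on Borg. This stands, and it limits the size of the point. It does not remove the contradiction over T0.

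It could also be said that Borg might be taken at the T0 walk test. Nothing in the article says so, and section 2.4.2 ties the rating to the video sessions.

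Some stronger readings are tempting, but the document does not support them:

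- *The missing control values break the model.* The first-aim model has no group factor. Restricted to the intervention arm, it needs no control rating. The absence of control values rules out a comparison of Borg between arms, which that sentence does not plan.
- *Borg change cannot be derived at all.* A T1 to T2 contrast within the intervention arm is possible once session ratings are assigned to those times, and such a rule may stand in a fuller plan.
- *A rise in Borg is bound to occur with unchanged adherence.* The move from 50% to 73% spans the whole programme; from T1 to T2 it is about 67% to 73%. Gains in fitness or choice of the easier level could offset it.
- *Collection is described in two conflicting ways.* A weekly form with one rating per session reads as a single method.
- *Heart rate should have been the intensity outcome.* It is recorded ("Moreover, their heart rate will be recorded") as part of the tracking feature. Not making it an outcome is no error, and using it by session would need session times that the article does not describe.

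**Conclusion.** The point holds in a narrow form. As written, the change in Borg across T0, T1 and T2 has no T0 data in any of the 300 planned women, so that analysis and its two post-hoc comparisons involving T0 cannot be carried out. This rests only on the article's own definitions of Borg and of T0.

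The wider consequence, that steps and IPAQ would also be left without cases, holds only if the three variables form one multivariate response and incomplete cases are deleted listwise. Otherwise the damage stops at Borg. The evidence on session intensity survives as session-level ratings in the intervention arm. The correction is inexpensive and worth making because the sentence concerned also carries the primary outcome.

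**What to change.** In section 3, delete the Borg scale from the variables analysed by the T0, T1 and T2 MANOVA, so that daily steps and IPAQ are analysed without it.

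State instead that the per-session Borg ratings will be summarised descriptively in the intervention arm only, by programme month and by the level chosen where a choice was offered. Give the number of ratings behind each summary, since ratings come only from women who did the sessions.

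The split by level assumes that the diary records which level was done; the article does not say so. If it does not, one diary item is needed, or the summary is by month alone. Section 2.3.2 (session 10) and Table 3 (week 12) also differ on when the choice begins, and the two should be reconciled before the split is defined.

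The cost is a change of wording and the loss of a formal test of Borg change, whose comparisons with T0 could not have been run. Sample size and the primary outcome definition are unaffected.

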### Study Aims

The primary goal of the Women’s Involvement in Steady Exercise (WISE) randomized controlled trial (RCT) is to evaluate the adherence to a six-month HIIT program, accompanied by nutritional plans and other health-related advice, delivered via a mobile application, among sedentary young women aged 15 to 24 years. This trial aims to determine the effectiveness of the exercise intervention by assessing the changes in the participants’ daily step count over the six-month period. The secondary objectives include analyzing the medium- and long-term effects of the program on various variables, including physical activity, anthropometric measurements, body composition, physical capacities, well-being and psychological mediators.

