### 2.4. Outcome Measures

#### 2.4.1. Primary Outcomes

The primary outcome of this study will be the change in daily steps from baseline to three months and six months. Daily steps will be assessed using the Xiaomi Mi Band 5 smartwatch, a reliable wearable activity tracker that has been validated in previous research [35,36,37]. Days with missing data, defined as days with fewer than 1000 steps, based on previous literature [38,39], will be excluded from the analysis [40,41] to ensure accurate and comprehensive data representation.

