Quality of sleep	Quality of sleep will be assessed with The Pittsburgh Sleep Quality Index (PSQI), a self-administered questionnaire used to evaluate sleep quality during the past month. The validity of the PSQI has been confirmed by several studies in different patient populations and languages [54,55,56,57]. The PSQI consists of seven clinically derived components that assess sleep difficulty, and the sum of these seven component scores yields a global score of subjective sleep quality [57]. The PSQI demonstrates moderate convergent validity compared to measures of insomnia and fatigue and good divergent validity with measures of daytime sleepiness and circadian phase preference in young adults [58].
Period pain	Pain intensity will be measured using the visual analogue scale (VAS). A 100-mm line bounded by “no pain” on the left (0) and “worst pain possible” (100) on the right will be used to indicate the average pain during the period. The minimum clinically detectable difference (MCID) of this scale has been set at 30 mm [59]. It is also a scale that has been validated [60].
Psychological mediators	
Perceived enjoyment	The Physical Activity Enjoyment Scale (PACES) is used to evaluate perceived enjoyment of physical activity during the intervention. The questionnaire comprises 16 items, where participants rate their feelings about the physical activity they have been engaging in using a 7-point Likert scale, ranging between 1 (not at all) and 7 (very much) [61]. PACES shows a very high internal consistency (Cronbach’s alpha = 0.908) and the test-retest reliability indicates a good temporary agreement (Spearman rho = 0.815, *p* < 0.001) in adolescents with overweight and obesity [62].
Program adherence	
Retention, Attendance, Duration and Intensity	These four variables will be used to measure program adherence, as described before.

WISE, Women’s Involvement in Steady Exercise; RCT, randomized controlled trial; BMI, body mass index; PPT, pressure pain threshold.

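### Section 3 answers the adherence aim with daily steps and IPAQ, which are not among the four criteria that define programme adherence, and with a T0-T1-T2 test that none of those criteria can enter

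*Protocol article*

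**What the plan says.** **The aim.** Under Study Aims, the primary goal "is to evaluate the adherence to a six-month HIIT program". The next sentence gives daily steps a different job: "This trial aims to determine the effectiveness of the exercise intervention by assessing the changes in the participants’ daily step count".

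**The definition.** Section 2.4.2 lists four criteria for programme adherence:
- Retention: "the participants following the WISE exercise videos and showing up to the follow-up measurements".
- Attendance: the share of the 50 videos that was completed.
- Duration: "adherence to a minimum of 20 min of exercise two times a week".
- Intensity: "intensity levels of the sessions will be assessed at the end of each session using the modified Borg Scale".

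The section takes them from a weekly online diary. Table 5 confirms the set in its programme adherence row: "These four variables will be used to measure program adherence, as described before".

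**Steps and IPAQ.** Section 2.4.1 states: "The primary outcome of this study will be the change in daily steps from baseline to three months and six months". Table 5 lists IPAQ as a secondary outcome under physical activity.

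**The analysis.** Section 3 says that the first aim will be answered by analysing "the changes in the adherence variables, such as daily steps, the Borg scale and the IPA questionnaire". The method is a MANOVA with one within-subject factor and Bonferroni-adjusted comparisons of T0, T1 and T2. Elsewhere in Section 3, the number of sessions completed is to be summarised by a median and a percentage achieved. Secondary outcomes go to a separate two-factor model with a group term.

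**The concern.** The article defines adherence one way and tests it another way. Two of the three variables that Section 3 calls adherence variables have that label nowhere else. Both measure general activity. A woman can walk more, or report more activity, without using the videos. She can also complete the home sessions with little change in her step count.

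At stake is the answer to the stated primary goal. A significant change over time in steps or IPAQ could be reported as good adherence to the HIIT programme, although the variables that record use of the programme were not part of the test. IPAQ would also be analysed twice, once as an adherence variable over time only and once as a secondary outcome with a group term. Its two results could be read as answering different questions.

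**Working it through.** No sample-size or power figure is involved. The check sets the definition beside the analysis and asks which variables the stated test can handle.

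**Step 1. Which variables are on which list?** Roles come from Sections 2.4.1 and 2.4.2 and Table 5. The analysis list comes from Section 3. Availability at T0 is worked out in step 2.

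| Variable | Role in 2.4 and Table 5 | Named for the first aim in Section 3 | Value at T0 |
|---|---|---|---|
| Retention | adherence criterion | no | no |
| Attendance | adherence criterion | no | no |
| Duration | adherence criterion | no | no |
| Intensity (Borg) | adherence criterion | yes | no |
| Daily steps | primary outcome | yes | yes |
| IPAQ | secondary outcome | yes | yes |

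- Named variables that are defined criteria: 1 of 3 (Borg).
- Defined criteria that are not named: 4 − 1 = 3 of 4.

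**Step 2. Can the criteria enter a T0-T1-T2 comparison?**
- Section 2.3.1 places T0 before the intervention starts, and Section 2.2.4 places randomisation after T0. At T0 no woman has an allocation or a video.
- Attendance counts videos completed, so it does not exist at T0.
- Section 2.4.2 judges duration from the diary question on whether both weekly video sessions were done, so it does not exist at T0 either.
- Retention concerns following the videos and returning for later visits. It has no baseline.
- Borg is scored at the end of each session, so there is no T0 score.
- Result: 0 of 4 criteria have a T0 value. For Borg, a T1 versus T2 comparison is the most that the stated test could give.

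**Step 3. What remains?** Section 2.4.1 defines steps as change from baseline, and Table 1 schedules IPAQ at T0, T1 and T2. These are the only two named variables for which the T0 comparisons can be made, and neither is a defined adherence criterion.

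**Step 4. In which arm does adherence exist?** Table 4 gives the videos to the intervention arm and opens them to controls only after the programme ends. During the trial, attendance, duration and session Borg are therefore intervention-arm quantities, whereas steps and IPAQ are collected in both arms.

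**The case against.** Several points on the other side have force.

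- **The list is open.** Section 3 introduces its variables as examples. A reader might infer that retention, attendance and duration are excluded, but the text does not say so. That part of the objection stands. It does not rescue the analysis, because step 2 shows that these criteria cannot enter the stated test even if they were added to the list.
- **Borg is a real adherence criterion.** A reader might infer that none of the named variables measures use of the programme. That is wrong for Borg, which is the intensity criterion. Borg does describe how hard the completed sessions felt, not how many were completed.
- **Attendance will be reported.** Sessions completed get a median and a percentage, so it would be wrong to say that the trial will hold no attendance result. What is missing is the link: Section 3 assigns the first aim to the MANOVA, not to this summary.
- **Steps and IPAQ are not unrelated to the programme.** Table 2 includes a monthly step goal, feedback on daily steps and push notifications. IPAQ covers moderate and vigorous activity, so video sessions may raise it. A reader might infer that these measures hardly depend on the intervention. The documents do not support that, and they give no figure for how many steps a video session adds. The narrower statement holds: both can move without use of the videos.
- **Adherence is also used broadly.** The Introduction describes lack of adherence as not keeping up some form of physical activity, and the Conclusions speak of exercise adherence. Steps fit that wider sense. But the Study Aims name adherence to the HIIT programme, and Section 2.4.2 and Table 5 define it.

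The absence of a group term from the first-aim model is a separate matter and adds nothing to this point.

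**Conclusion.** The point holds in a limited form. Section 3 contradicts Section 2.4.2 and Table 5 on what adherence is, and its T0-T1-T2 test cannot assess any of the four defined criteria as written. The T0 comparisons offered as the answer to the adherence aim would come from steps and IPAQ alone. The size is the count given above: 1 of 3 named variables on the defined list, 3 of 4 criteria not named, and 0 of 4 with a T0 value. No effect on power or on an estimate can be derived from the documents.

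The conclusion rests on two readings. The first aim in Section 3 is taken to be the primary goal under Study Aims, and programme adherence is taken as Section 2.4.2 defines it. This is not a defect in data collection, because the diary already captures what is needed. It should be corrected before analysis, since it decides what the trial's stated primary goal is judged on.

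**What to change.** In Section 3, replace the first-aim sentence with an analysis of the four criteria in Section 2.4.2, estimated in the intervention arm over all women randomised to it (150 planned), each with a 95% confidence interval:

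1. Retention, as the proportion retained.
2. Attendance, as the percentage of the 50 videos completed.
3. Duration, as the percentage of weeks that meet the rule of 20 minutes twice a week. At two videos a week, 50 videos span 50 / 2 = 25 weeks.
4. Intensity, as session Borg among the sessions done.

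State that the planned summary of sessions completed belongs to this aim. Remove steps and IPAQ from the adherence analysis. Analyse steps as the primary effectiveness outcome, and IPAQ once, as a secondary outcome compared between arms.

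The cost is rewording and a few extra estimates from data already planned. The drawback is that the adherence aim becomes a one-arm estimate without a significance test, and it depends on self-reported diary entries.
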